## Abstract

**Background:**

One third of all cancer patients will develop bone metastases and the vertebral column is involved in approximately 70% of these patients. Conventional radiotherapy with of 1–10 fractions and total doses of 8-30 Gy is the current standard for painful vertebral metastases; however, the median pain response is short with 3–6 months and local tumor control is limited with these rather low irradiation doses. Recent advances in radiotherapy technology – intensity modulated radiotherapy for generation of highly conformal dose distributions and image-guidance for precise treatment delivery – have made dose-escalated radiosurgery of spinal metastases possible and early results of pain and local tumor control are promising. The current study will investigate efficacy and safety of radiosurgery for painful vertebral metastases and three characteristics will distinguish this study. 1) A prognostic score for overall survival will be used for selection of patients with longer life expectancy to allow for analysis of long-term efficacy and safety. 2) Fractionated radiosurgery will be performed with the number of treatment fractions adjusted to either good (10 fractions) or intermediate (5 fractions) life expectancy. Fractionation will allow inclusion of tumors immediately abutting the spinal cord due to higher biological effective doses at the tumor - spinal cord interface compared to single fraction treatment. 3) Dose intensification will be performed in the involved parts of the vertebrae only, while uninvolved parts are treated with conventional doses using the simultaneous integrated boost concept.

**Methods / Design:**

It is the study hypothesis that hypo-fractionated image-guided radiosurgery significantly improves pain relief compared to historic data of conventionally fractionated radiotherapy. Primary endpoint is pain response 3 months after radiosurgery, which is defined as pain reduction of ≥ 2 points at the treated vertebral site on the 0 to 10 Visual Analogue Scale. 60 patients will be included into this two-centre phase II trial.

**Conclusions:**

Results of this study will refine the methods of patient selection, target volume definition, treatment planning and delivery as well as quality assurance for radiosurgery. It is the intention of this study to form the basis for a future randomized controlled trial comparing conventional radiotherapy with fractionated radiosurgery for palliation of painful vertebral metastases.

**Trial registration:**

ClinicalTrials.gov Identifier: NCT01594892

## Background

### Conventional palliative radiotherapy for painful vertebral metastases

Approximately one third of all patients with cancer will develop bone metastases
[1] and of these patients, approximately 70% will have metastases involving the vertebral column, most commonly the thoracic and lumbar spine. Radiation therapy plays an important role in the multidisciplinary treatment of symptomatic vertebral metastases, including palliation of pain, control or prevention of neurological symptoms, and prevention of pathologic fractures.

During the past three decades, the gold standard of radiotherapy for painful bony metastases has been based on several randomized trials comparing various radiotherapy fractionation schemas: the majority of the studies compared single fraction radiotherapy of 8 Gy with fractionated protocols of 5–10 fractions and total doses of 20-30 Gy (meta-analyses in
[2,3]). Radiotherapy was effective with overall pain relief in 70% of the patients on average. No dose–response relationship has been demonstrated in the meta-analyses meaning that increased irradiation doses delivered in multiple fractions did not result in higher pain response rates than a single fraction of 8 Gy and this palliative regime is consequently the evidence-based standard of care
[4].

Nevertheless, there are clinical data suggesting that patients with painful vertebral metastases might benefit from higher irradiation doses than used in the prospective trials cited above. Despite overall pain response being high at 70%, the median duration of pain response is only 3 – 6 months. Consequently, only approximately 1/3 of the patients are effectively palliated for a duration of a few months with these conventional radiotherapy schemas. Additionally, partial pain response should not be the primary goal of treatment but rather complete pain response, which is achieved in only one quarter of the patients.

Studies on metastatic spinal cord compression (MSCC) confirm that conventional irradiation doses might not be sufficient for intermediate or even long term local disease control. Patchell et al. reported a randomized trial comparing radiotherapy alone with decompressive surgery followed by radiotherapy
[5]; radiotherapy consisted of ten fractions of 3 Gy. Maintenance of walking ability was achieved for a median duration of 13 days and 122 days in the radiotherapy alone arm compared to combined treatment indicating that intensification of local treatment improved the outcome. Another randomized study compared lower and higher dose radiotherapy for MSCC
[6]. Whereas no difference in response rates was observed for the total patient population, significantly improved response after high dose compared to low dose irradiation was observed in the subgroup of patients with unfavourable histologies (lung, kidney, gastrointestinal, head and neck, melanoma and sarcoma); a dose response relationship was not observed in patients with favourable histologies (lymphoma, seminoma, breast, prostate, myeloma). This again indicates that subgroups of patients might benefit from intensified local radiotherapy in this palliative setting.

Diagnostic possibilities and systemic treatments have significantly evolved in the recent years, with many patients surviving a metastatic state for years, which increases the need for more effective treatment of spinal metastases. Furthermore, prognostic scoring systems are available, which allow selection of patients with favourable traits
[5-7]. These patients with life expectancy longer than 3 – 6 months might benefit from or even require a radiotherapy treatment offering more durable pain control, maintenance of quality-of-life and of neurological function.

### Radiosurgery for painful vertebral metastases

Stereotactic radiosurgery for intracranial metastases delivered either with or without whole brain radiation therapy, has been associated with very high rates of local tumour control, in the range of 85-95% across studies
[7-12]. This stereotactic radiosurgery not only improved local tumor control but also overall survival when practiced in patients with a solitary brain metastasis. These results, in conjunction with very low complication rates related to the highly conformal nature of the treatment, have made intracranial radiosurgery an increasingly popular and available treatment modality.

Irradiation with such escalated “radiosurgical” doses has not been possible for spinal metastases because of the anatomical situation, where the tumor is very close to the spinal cord and frequently even wrapped around this critical organ-at-risk. Traditional technologies made it impossible to achieve a sufficiently high irradiation dose in this complex shaped target volume while simultaneously keeping the dose to the spinal cord within accepted tolerances
[13]. Two recent advances in radiotherapy technologies have made it possible to transfer the radiosurgical concept from the brain to the vertebral region. Intensity-modulated radiotherapy (IMRT) allows the generation of convexly shaped dose distributions sparing the spinal cord from high irradiation doses. Image-guided (IGRT) verification of patient set-up enables accurate delivery of the planned dose distributions, which is especially important from a safety perspective because of the steep dose gradients between the target and the spinal cord.

In a recent survey, more than 40% of all radiation oncologists in the US stated that they practice spine radiosurgery and most institutions favour single-fraction radiosurgical techniques due to best patient comfort with a “one-shot” outpatient treatment in the context of limited life expectancy
[14]. Rapid adoption of spinal radiosurgery is observed despite the paucity of prospective trials. Only one prospective study has been published so far
[15] and the randomized RTOG 0631 is still accruing patients. Nevertheless, results of these radiosurgical studies are promising: local tumor control / pain control has been reported in 80-90% of the patients and this was achieved with low rates of severe toxicity
[15-20]. The most serious toxicity – radiation induced myelopathy – has been reported in less than 1% of the patients in a large analysis of > 1000 treatments
[21].

The concept of radiosurgery practiced as single fraction, however, has limitations. Due to the immediate proximity of vertebral metastases to the spinal cord, the treatment dose deliverable is limited by the tolerance of the spinal cord
[21-24]. In cases of radiosurgical treatment of these spinal cord abutting tumors, the epidural tumor component has been identified as the most frequent site of treatment failure: both the spinal cord and adjacent epidural tumour involvement were spared from high biological doses of radiosurgery
[16-18,25,26]. Consequently, many study protocols exclude tumors within a distance of < 3 mm to the spinal cord, as does the RTOG 0631 trial. This however precludes exactly those patients which are at the highest risk of cord compression.

### Rationale for this trial

The rationale for this trial is based on the same hypothesis as the single-fraction radiosurgical studies: to improve pain control and local tumor control via dose intensified radiotherapy for vertebral metastases. This trial will differ in three important aspects from the currently available literature and trials:

1) A prognostic score for overall survival (modified Mizumoto Score) will be used for selection of patients with favourable life expectancy
[27], who are expected to benefit most from the intensified radiotherapy. The number for treatment fractions will be adjusted based on the modified Mizumoto Score to balance intensity and length of treatment with life expectancy. Selection of patients with long life expectancy will also allow for evaluation of late toxicity and long-term efficacy.

2) Hypo-fractionated radiosurgery with 5 and 10 treatment fractions will be practiced in this study. Based on radiobiological modelling, hypo-fractionated radiosurgery allows higher biologically effective doses to the tumor directly adjacent to the spinal cord than single-fraction protocols. Recurrences at the interface between the spinal cord and the epidural tumor are expected to be reduced by fractionation. This will expand the indications for dose intensified radiotherapy to tumors immediately abutting the spinal cord.

3) Failures in untreated parts of the vertebrae shall be avoided by the use of a simultaneous integrated boost concept. Similar to the single-fraction radiosurgical studies, dose intensification will be performed in the macroscopic tumour using dedicated CT and MR imaging. However, the non-involved parts of the vertebra will be treated with a second dose level (conventional dose) to avoid recurrences in the untreated parts of the vertebrae.

Preliminary results from the University Hospital Wuerzburg with dose intensified irradiation using 20 fractions of 3 Gy
[28] are promising and support the hypothesis of this trial; Patients with long life expectancy were selected for fractionated radiosurgery resulting in an actuarial local control rate and overall survival of 88% and 63% after 2 years
[13]. No acute or chronic toxicity > Grade 2 was seen.

## Methods/design of the trial

### Study design

The study is designed as a prospective phase II trial. The outline of the study protocol is shown in Figure
1.

**Figure 1 F1:**
[figure not shown]
Design of the DOSIS study.

### Study hypothesis

Hypo-fractionated image guided radiosurgery significantly improves pain relief compared to historic data of conventionally fractionated radiotherapy.

### Primary endpoint

The primary objective is to determine whether a sustained pain relief can be achieved with dose intensified hypo-fractionated image-guided radiosurgery in patients with vertebral metastasis and intermediate and long life expectancy based on the modified Mizumoto Score. The Mizumoto score is slightly modified to improve overall survival in the group with intermediate life expectancy. Pain response 3 months after radiosurgery will be evaluated as primary endpoint and pain reduction of ≥ 2 points at the treated vertebral site on the 0 to 10 Visual Analogue Scale without analgesic increase will be defined as pain response
[29].

### Secondary endpoints

1. Local tumor control at the treated vertebral levels and regional tumor control at the neighbouring vertebrae

2. Overall survival and cancer specific mortality

3. Quality of life using the EQ-5D and EORTC QLQ-BM22

4. Acute and late toxicity according to NCI CTCAE v 4.0

### Exploratory endpoints

1. Time between initial consult and first treatment (the goal is to reduce this period to within 48 hours by maximizing use of standardized procedures of diagnostics, fixation and planning)

2. Repositioning and image-guidance accuracy within the fixation system in six degrees of freedom

3. Intra-fraction motion as analysed by comparison of cone-beam CT imaging immediately preceding treatment

4. Morphological pattern of CT and MRI radiological response of vertebral metastases after dose-intensified, hypo-fractionated radiosurgery

### Inclusion criteria

Patients with the following characteristics will be eligible for this study

1. Established histological diagnosis of a malignant tumour (primary or metastatic)

2. Vertebral metastasis confirmed via biopsy or radiology

3. Pain in the involved spinal region or free of pain under pain medication

4. Fully consenting patients, > 18 years old

5. Karnofsky Performance Index ≥ 60%

6. Good or intermediate life expectancy according to the modified prognostic Mizumoto Score (score ≤ 9)

7. Patient must be able to tolerate fixation systems and 30 minutes treatment time

8. Discussed in interdisciplinary tumour board

9. The following types of spinal tumours are eligible:

Recurrent / residual tumours after surgery

Tumours in medically inoperable patients or patients deemed inoperable due to limited life expectancy / tumour load

Lesions associated with significant surgical risk

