**Table 2 T2:** **Patient follow**-**up and assessment scheme**

**Assessment**	**Prior RT**	**weekly during RT**	**Post RT**	**1**-**4 weeks**	**6 weeks**	**3 mon**	**6 mon**	**9 mon**	**12 mon**	**18 mon**	**24 mon**
**Physical Examination**	X	X	X		X	X	X		X		X
**Karnofsky performance index**	X	X	X		X	X	X		X		X
**Documentation of Pain** &**Analgesic Use**	X	X	X	Self assessment	X	X	X	Tel.	X	Tel.	X
**EQ**-**5D**	X	X	X		X	X	X		X		X
**QLQ**-**BM22**	X	X	X		X	X	X		X		X
**NCI CTCAE v4 toxicity**		X	X		X	X	X		X		X
**MRI** / **CT imaging**	X				X	X	X		X		X

Tel: patients will be interrogated by a study nurse via telephone.

Self-assessment: patients will be given letters for self-assessment of pain and analgetic use for the four weeks following radiosurgery.

For evaluation of pain a 10 point visual analogue scale will be used
[15] and analgesic use will be recorded. Pain response is defined as a reduction of ≥ 2 points at the treated site without analgesic increase. Complete pain response is defined as a pain score of 0 at the treated site with no concomitant increase in analgesic intake. Stable pain is defined as unchanged score or within 2 points of the baseline with no increase in analgesia.

Quality of life will be analysed using the EQ-5D and EORTC QLQ-BM22 questionnaires.

Local control will be defined by repeat imaging (preferably MRT or CT). Progression events are defined as radiological documented disease progression using RECIST-Criteria (Revised Guidelines, Version 1.1, 2009)
[30].

Kaplan Meier curves for local tumor control, cancer specific survival and overall survival will be calculated starting from the first day of treatment.

This study will use the International Common Terminology Criteria for Adverse Events (CTCAE) version 4.0 for toxicity and adverse event reporting.

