#### Sample size calculation

This study aims to demonstrate an improvement in pain control at 3 months from approximately 40-50% with conventionally fractionated radiotherapy to 70-80% with image-guided, hypo-fractionated radiotherapy. Assuming an improvement in pain control from 45% to 75% sample size calculations at a 5% statistical significant level show that 27 patients would be required to achieve power of the study of 90%. This is the total number of patients eligible for statistical analysis per study arm, i.e. 54 in total. Considering a 10% drop-out rate, the total number of patients is 60. No comparison will be made between the two study arms.

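### Eligible patients with a baseline pain score below 2 cannot meet the primary endpoint, and the plan's own pain definitions classify them in conflicting ways

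*Protocol article*

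**What the plan says.** Under Inclusion criteria, item 3 of the protocol article accepts "Pain in the involved spinal region or free of pain under pain medication". Neither the inclusion nor the exclusion list sets a minimum pain score.

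Under Primary endpoint, response at 3 months is "pain reduction of ≥ 2 points at the treated vertebral site on the 0 to 10 Visual Analogue Scale without analgesic increase". The text after Table 2 repeats this rule and adds two categories:

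- The first looks only at the final score: "Complete pain response is defined as a pain score of 0 at the treated site with no concomitant increase in analgesic intake".
- The second covers little or no change from entry: "Stable pain is defined as unchanged score or within 2 points of the baseline with no increase in analgesia".

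No category credits a reduction in analgesics.

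The Sample size calculation section reads "Assuming an improvement in pain control from 45% to 75" (per cent), with "sample size calculations at a 5% statistical significant level", and finds that "27 patients would be required to achieve power of the study of 90" (per cent). It continues: "This is the total number of patients eligible for statistical analysis per study arm, i.e. 54 in total". The only inflation is 10% for drop-out, which brings the total to 60. The section sets no baseline-pain condition for the analysed set.

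**The concern.** A fall of at least 2 points is arithmetically impossible from a baseline of 0 or 1. The eligibility rule expressly admits patients at 0 on medication, so the trial can enrol patients whose primary outcome is fixed at entry whatever the treatment does.

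The complete-response rule looks only at the final score and requires no fall. The same patient can therefore be a complete responder, stable, and not a responder. Complete response is then not a subset of response.

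If such patients are enrolled, the observed primary rate depends on case mix at entry as well as on treatment. Whether this hides a true effect or favours a false one depends on which definition is applied to them. If that choice is left open until results are known, the data can drive it.

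**Working it through.** **Inputs.** From Sample size calculation: p0 = 0.45, p1 = 0.75, 5% level (sidedness not stated), 90% power, 27 per arm. The share f of patients with a baseline score below 2 is not in the document. It is an assumption, shown at 5%, 10% and 20%.

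**1. Reproduce the plan's figure.** One-sample test of a proportion, normal approximation, two-sided 5%:

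n = [(z_α√(p0(1−p0)) + z_β√(p1(1−p1))) / (p1−p0)]²
= [(1.960 × 0.4975 + 1.2816 × 0.4330) / 0.30]²
= (1.530 / 0.30)² = 26.01, rounded up to 27.

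The approximate power at 27 is 91.1%. A one-sided test would need 21 (20.95), so the plan's 27 fits a two-sided test. Then 2 × 27 = 54, and 54 / 0.9 = 60. The stated figures reproduce.

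**2. Exact test at n = 27 against 45%.** Rejecting at 18 or more responders has upper-tail probability 0.0193 (two-sided 5%). Rejecting at 17 or more has 0.0464 (one-sided 5%).

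**3. Patients below 2 counted as non-responders.** The attainable rate is 0.75 × (1 − f).

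| f (assumed) | Attainable rate | Power, reject at ≥18 | Power, reject at ≥17 |
|---|---|---|---|
| 0 | 75% | 88.7% | 94.7% |
| 5% | 71.25% | 77.4% | 87.6% |
| 10% | 67.5% | 62.5% | 76.4% |
| 20% | 60% | 30.9% | 45.9% |

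With a fixed number of such patients among 27 and the cut-off at 18, power is 82% with one and 61% with three.

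**4. Excluded without replacement.** Normal approximation, two-sided: 91.1% at 27, 90.0% at 26, 87.3% at 24, 84.1% at 22. Exact power moves in steps because the cut-off is a whole number. At 24 it is 76.6% (reject at ≥17, tail 0.0095) and at 22 it is 83.8% (reject at ≥15, tail 0.0243). With three such patients, exclusion still costs less than counting them as failures (exact 76.6% against 60.7%).

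**5. Counted as responders through the complete-response wording.** With a true 45% among patients who can respond, k automatic responders and the cut-off at 18, false success is P(Bin(27−k, 0.45) ≥ 18−k). This is 1.9% for k = 0, 6.5% for k = 3 and 13.3% for k = 5.

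**6. Excluded and replaced.** Keeping 54 evaluable needs 54 / (0.9 × (1 − f)) enrolled: 64, 67 and 75 at f = 5%, 10% and 20%, against 60 planned.

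**The case against.** A reader might infer that the stated 90% power is lost. The document does not support that as a fact. It gives no figure for how many patients will enter below 2, and it sizes the trial on patients eligible for statistical analysis, a set that could exclude them. Analysis sets are often left to a full protocol or analysis plan, and neither is shown. If these patients are excluded, they are not failures and the loss is modest.

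A reader might also infer that the error always runs against the treatment. It does not: under the complete-response wording it runs the other way.

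Other points on this side are fair. The sample size arithmetic is correct. Complete response is neither the primary endpoint nor in the list of secondary endpoints. Admitting pain-free patients makes sense for local control, survival, toxicity and quality of life, so the inclusion criterion is not itself a mistake. The Sample size calculation section does not describe the case mix behind its 45%, so a firm statement that the historic comparison is not like for like would go too far.

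These points limit the size and certainty of the concern but do not remove it. The eligibility rule and the pain definitions are both stated in the article and do not fit together, so this is more than detail left to another document. Nothing stated keeps patients below 2 out of the analysed set, and the enrolment target allows only for drop-out.

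**Conclusion.** The point stands in conditional form. As written, a patient with a baseline score below 2 is eligible, cannot respond on the primary endpoint, and can at the same time be a complete responder and stable. That follows from the text and needs no assumption.

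The numerical consequence rests on two things the article does not give: the share of such patients and how they are counted. The planned 27 per arm leaves little reserve, so even one or two per arm matter if they count as failures. Exclusion costs less. Counting them as responders inflates false success instead. These figures treat each arm as a separate one-sample test, as the per-arm sizing implies. The rule should be settled before outcomes are examined.

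**What to change.** Define the primary analysis set as treated patients with a baseline score of at least 2 at the treated site. Count the 27 per arm on that set, or restate the power at the number obtained. Require a fall of at least 2 points from baseline for complete response, so that it becomes a subset of response. Keep patients with a baseline below 2 in the trial for local control, survival, toxicity and quality of life.

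This is a one-paragraph amendment that leaves treatment and eligibility unchanged. The cost is that fewer enrolled patients count towards the primary endpoint. Either power is somewhat lower than stated, or enrolment rises above 60 as in step 6 of the working.
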